#### Focus groups (qualitative data)

The qualitative focus group data will be analysed by two members of the research team with qualitative expertise using inductive thematic content analysis consistent with an interpretive descriptive approach. Data will be entered into NVivo. Transcribed data will be coded first by using an open coding process to organise the data by identifying broad thematic patterns [28]. The data will then be read and re-read to enable classification into categories and specific themes [28, 29].

#### Psychometric properties of screening tools

To examine the psychometric properties of the EPDS, ‘Whooley’ questions, GAD-2 and MGMQ when used during pregnancy (Secondary Aim), we will conduct a receiver operator curve analysis to calculate the area under the curve and sensitivity, specificity, positive and negative predictive values and positive and negative likelihood ratios negative likelihood ratios of each measure, using the M.I.N.I. as the gold standard (mood and anxiety disorder modules only). Consistent with other studies of this type a value of 0.5 will be added if a 2x2 cell contains zero, in order to calculate the likelihood ratios and associated confidence intervals. In addition the various screening measures will be compared with each other, using each measure’s screen-positive threshold (where these thresholds are available).

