^b^‘Complex’ risk factors : homelessness or housing instability; domestic violence; substance misuse; contact with child protection services

^c^‘Social’ risk factors: young maternal age (less than 20 years); no partner; booking-in appointment at >20 weeks gestation

**Table 2 Tab2:** Data collection schedule and measures

Measure	Time 1 *All women (routinely collected data)*	Time 2 *Consenting women only*	Time 3 *Health professionals only*
Demographic information^a^	X		
EPDS^a^	X	X	
Psychosocial assessment^a^	X		
Routine referral information^b,c^	X		
Feedback survey (women)^d^		X	
Costing data	X		X
Feedback survey; observational data; key informant interviews; focus groups (health professionals)^b,c,e^			X
Whooley questions^f^		X	
GAD-2^f,g^		X	
MGMQ^f,g^		X	
MINI^f,g^		X	
Interval question^f,g^		X	
Brief help seeking items^f,g^		X	

*EPDS* Edinburgh Perinatal Depression Scale, *GAD-2* Generalized Anxiety Disorder Scale-2items, *MGMQ* Matthey Generic Mood Questionnaire, *MINI* Mini International Neuropsychiatric Interview (v6.0; mood and anxiety disorder modules only; Data will be used to address: ^a^All aims; ^b^Primary Aim 1 (clinical effectiveness); ^c^Primary Aim 2 (cost effectiveness); ^d^Primary Aim 3 (pregnant women perspectives); ^e^Primary Aim 3 (health care provider perspectives); ^f^Secondary Aim (psychometric evaluation). ^g^Completed by women allocated to the PIPA model of care only

*Primary Aim 2: Cost-effectiveness outcomes:* To quantify: i) the cost per ‘correct’ and ‘incorrect’ referral made at the initial psychosocial assessment, for each model of care; ii) the incremental cost per ‘correct’ referral made and the incremental cost per ‘incorrect’ referral averted by the PIPA model compared to the SAFE START model; and, iii) the budgetary implications of implementing the PIPA model at the participating site, based on number of women assessed.

*Primary Aim 3: Consumer perspectives:* To compare the acceptability and perceived benefit of each model of care from the perspective of both pregnant women and their healthcare providers.

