*Secondary Aim: Psychometric properties of screening tools:* To examine the sensitivity, specificity, positive and negative predictive values, and positive and negative likelihood ratios of the EPDS [6], ‘Whooley’ depression questions [19, 20], the Generalized Anxiety Disorder Scale [GAD-7] and its short form [GAD-2] [21], and Matthey Generic Mood Questionnaire (MGMQ) [22] when used during pregnancy, using the Mini International Neuropsychiatric Interview v6.0 [23] (MINI) as the gold standard.

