### Data sources, measures and procedures

#### Time 1: Initial psychosocial assessment conducted at the antenatal ‘booking in’ visit

The hospital data management system (ObstetriX and subsequently eMaternity) will be used to identify all women who attended the participating site during the data collection periods for the PIPA Project, and for whom a routine psychosocial assessment was completed. The Time 1 dataset will include: date of booking in visit and psychosocial assessment; gestation and maternal age at this time; maternal date of birth; estimated date of delivery; partner status; gravidity (including reason for pregnancy loss, where available); parity; country of birth; physical health conditions; type of conception; model of maternity care; EPDS: total and Q10 scores; EPDS: item level responses (SAFE START only); psychosocial questions: item level responses; psychosocial questions: total score (PIPA only); referral/s indicated as a result of the psychosocial assessment (yes/no); referral/s indicated as a result of the psychosocial assessment (specified; PIPA only); language; interpreter needed; financial class (public, private or overseas patient); and Time 2 Expression of Interest response (yes/no). Time 1 data will be extracted by the data manager at the participating site at approximately weekly intervals, for all women allocated to the SAFE START and PIPA models of care.

#### Time 2: Two weeks post-time 1

Women who consent to participation at Time 2 will complete the EPDS [6], the ‘Whooley’ questions [19] followed by a third ‘help’ question [20], the Generalized Anxiety Disorder Scale [GAD-7] [21], the Matthey Generic Mood Questionnaire (MGMQ) [22], an ‘interval’ question to assess perceived change in emotional wellbeing at Time 2 [27] and the Mini International Neuropsychiatric Interview v6.0 [M.I.N.I.; mood and anxiety disorder modules only] [23]. Women will also complete a short survey covering the acceptability of the psychosocial questions and assessment process.

‘Key Survey’™ will be used as the platform for data collection for all Time 2 measures *except* the M.I.N.I., which will be collected using infrastructure provided by Medical Outcomes Systems (to whom the online M.I.N.I. is copyrighted). Alternatively, these questionnaires will be administered by phone by the Research Officer verbatim, with participant responses captured in the project-specific ‘Key Survey’ and MINI instruments.

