## Abbreviations

ANRQ-R: Antenatal risk questionnaire-revised
EPDS: Edinburgh perinatal depression scale
GAD-2: Generalized anxiety disorder scale-2 items
M.I.N.I.: Mini international neuropsychiatric interview (v6.0)
MCD: Multidisciplinary case discussion meeting
MGMQ: Matthey generic mood questionnaire
PIPA: Perinatal integrated psychosocial assessment

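### The secondary aim and the Time 2 procedures name the GAD-7, but Table 2 schedules and the analysis evaluates only the GAD-2

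*Protocol article*

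**What the plan says.** Four parts of the protocol article decide which anxiety scale is collected and analysed.

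- **Aims, Secondary Aim.** The tools to be evaluated against the MINI include "the Generalized Anxiety Disorder Scale [GAD-7] and its short form [GAD-2", alongside the EPDS, the Whooley questions and the MGMQ. That makes five tools. For each, the aim promises sensitivity, specificity, predictive values and likelihood ratios.
- **Time 2: Two weeks post-time 1.** The measures that consenting women complete include "the Generalized Anxiety Disorder Scale [GAD-7] [21], the Matthey Generic Mood Questionnaire (MGMQ) [22], an ‘interval’ question". The GAD-2 is not named.
- **Table 2, data collection schedule.** There is a GAD-2 row at Time 2 and no GAD-7 row. The footnote defines only "Generalized Anxiety Disorder Scale-2items". It tags the row as serving the secondary aim and as completed only by women in the PIPA model. The MINI row carries the same tags.
- **Statistical analysis, Psychometric properties of screening tools.** The ROC and accuracy analysis covers the EPDS, the Whooley questions, "GAD-2 and MGMQ when used during pregnancy (Secondary Aim"). The GAD-7 is absent.

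The abbreviation list likewise has only "GAD-2: Generalized anxiety disorder scale-2 items".

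**The concern.** The procedures text and the schedule name different instruments for the same visit, and the analysis section omits a tool that the aim names. Someone building the Time 2 questionnaire from Table 2 would programme two items; someone building it from the procedures text would programme seven. An analyst working from the analysis section would report four tools, whereas a reader of the aim expects five.

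At stake is the GAD-7 part of the secondary aim. The two GAD forms are the only tools in the set named specifically for anxiety, and the Discussion presents evidence on both depression and anxiety screening in pregnancy as a contribution of this aim. Under Study status, SAFE START data collection is complete and PIPA collection has yet to begin. When the article was written, the choice of instrument was therefore still open in the one group that supplies these data.

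**Working it through.** No sample size, power or error rate enters this point, so the check sets the mentions of the two scales side by side.

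| Place in the article | GAD-7 named | GAD-2 named |
|---|---|---|
| Secondary Aim | yes | yes |
| Time 2 procedures | yes | no |
| Table 2 row and footnote | no | yes |
| Psychometric analysis | no | yes |

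The GAD-7 appears in 2 of the 4 operative places and the GAD-2 in 3 of the 4.

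**If Table 2 governs collection.** Taking the item counts from the scale names, 7 − 2 = 5 items are never asked. The GAD-7 total cannot be rebuilt from the two items that are. Under Participant eligibility and expected sample sizes, Time 2 is expected to enrol 1300 women, 650 per model. Table 2 restricts both the GAD row and the MINI to the PIPA model, so the women affected are the 650 in that group. The SAFE START women cannot fill the gap, because by Table 2 they receive neither the GAD items nor the reference standard.

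**If the Time 2 text governs collection and the analysis section governs analysis.** All seven items are collected. The GAD-2 can be scored from them, since the aim describes it as the short form. The tools analysed are then EPDS, Whooley, GAD-2 and MGMQ: 4 of the 5 in the aim. The GAD-7 has no ROC curve and no accuracy estimates in the section that sets out that analysis. It also drops out of the comparison between measures described there.

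**Can one reading make all four places true?** Reading the Table 2 entry as shorthand for the full scale would reconcile the schedule with the Time 2 text. It would not put the GAD-7 into the analysis list. Reading the GAD-2 as the only intended tool would reconcile Table 2 with the analysis, but it contradicts the aim and the Time 2 text. Neither reading removes the conflict.

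**The case against.** The strongest reply is that this is a naming slip with little consequence. The Time 2 section is the full procedural text: it says which measures women complete and how they are administered. Table 2 is a one-line-per-measure summary, so its entry may be shorthand. The aim already states the GAD-7's accuracy measures and its reference standard, and the analysis section refers back to that aim. The missing name may therefore be an oversight rather than a decision to drop the tool. If the seven items are collected, the GAD-7 can be analysed later by the same method, so only the Table 2 reading loses data for good. It is also possible that the investigators meant to evaluate the GAD-2 alone, in which case the aim and the Time 2 text need correcting.

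Much of this stands as a limit on the size of the problem. The irrecoverable loss belongs to one branch only, and the article does not show which text is the slip. None of it removes the contradiction. The analysis section is not silent on which tools it covers: it lists them, ties the list to the secondary aim, and leaves one out. An unseen analysis plan could settle the matter, but it could not make the four places in this article agree.

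**Conclusion.** The concern holds. The article contradicts itself on which anxiety scale is collected at Time 2, and its analysis covers four of the five tools in its secondary aim. Depending on which text is followed, either about 650 women have no GAD-7 score, permanently, or a collected GAD-7 has no analysis in the section written for it.

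The effect is confined to the secondary aim. The three primary aims do not use the scale, and the GAD-2 result is secure on either reading. This should be corrected, but it does not threaten the main comparison of the two models of care.

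The conclusion rests on three assumptions: the 650 is the article's anticipated number rather than an achieved one; the scale names give the item counts; and the two GAD-2 items are contained in the GAD-7, as the term short form in the aim implies.

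**What to change.** Follow the stated aim. Administer the GAD-7 once at Time 2 and score both the GAD-7 and the GAD-2 from it. In the text:

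1. Change the Table 2 row to GAD-7 (including GAD-2), and define both in the footnote and the abbreviation list.
2. Add the GAD-7 to the tools listed in the psychometric analysis, with the same ROC and accuracy measures against the MINI.
3. State in the Time 2 section that the GAD-2 is scored from the GAD-7 items.

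If the investigators in fact intend the GAD-2 alone, the aim and the Time 2 text must be changed instead, openly and before the data are seen.

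The cost is at most five short items per woman, or wording alone if the questionnaire already carries the full scale. The change belongs before PIPA data collection starts. If collection has already begun, first check which version was built into the survey platform.

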### Study status

This study is ongoing. Data collection for the SAFE START model of care (care as usual) is complete. Data collection for the PIPA model of care (alternative model) is scheduled to commence in the first half of 2017.

### Discussion

The value of an integrated approach to depression screening in facilitating the connection between assessment processes and care pathways has been demonstrated in the general population literature [30–32] and is gaining increased attention in the perinatal context [16, 33–35]. However, existing perinatal studies, like general population studies, have been limited to depression screening alone, rather than more comprehensive psychosocial assessment (which is inclusive of, but not limited to, depression screening). This is the first study of its kind to incorporate an evaluation of how broader components of integrated care, including electronic clinician decision-making aids and referral processes, may influence the outcomes of a program.

The PIPA Project will contribute substantially to the literature by providing evidence for the value of structured psychosocial assessment tools and electronic decision making algorithms in a large scale study. The present study will provide crucial insight into the most cost-effective use of health resources and information about potential sources of cost reduction (via improved resource efficiency in the public maternity sector). Through its secondary aim, the PIPA Project will also respond to calls made in the Australian and UK Clinical Practice Guidelines for further research evaluating the psychometric properties of screening tools for depression and anxiety in pregnant women.

## Abbreviations

ANRQ-R: Antenatal risk questionnaire-revised
EPDS: Edinburgh perinatal depression scale
GAD-2: Generalized anxiety disorder scale-2 items
M.I.N.I.: Mini international neuropsychiatric interview (v6.0)
MCD: Multidisciplinary case discussion meeting
MGMQ: Matthey generic mood questionnaire
PIPA: Perinatal integrated psychosocial assessment
